**Materials/methods:**

This is an open-label, single-arm phase 2 trial. Eligible patients have metastatic melanoma with ≤10 extracranial oligoprogressive sites while on first-line systemic therapy. Oligoprogression is defined using modified RECIST 1.1 or PERCIST criteria. All oligoprogressive sites will receive SBRT per institutional guidelines, typically delivered over 3 fractions. Patients will stay on current systemic therapy. The primary endpoint is PFS defined as the time from enrollment to the date of further disease progression. Secondary endpoints include overall survival, time on current systemic therapy, out-of-field response, tolerance of SBRT, and quality of life (QOL). In addition, serial blood samples are collected for exploratory analyses of circulating tumor DNA (ctDNA), mutant allele fraction, and immune profiling (including CD8+ T-cell subsets). The trial aims to enroll 52 patients over 12 months with additional 24 months of follow-up.

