**Figure 1 f1:**
[figure not shown]
CURB-Melanoma Trial Schema.

Primary Endpoint:

Progression-free survival - defined as time from enrollment to further disease progression (assessed by modified RECIST) or death from any cause.

Secondary Endpoints:

Overall survival - defined as the time from study enrollment to death from any cause.Time on current systemic therapy before switching to second line therapy - captures the duration from initiation of the current systemic therapy to the start of second-line treatment.Toxicity - treatment-related adverse events will be assessed and graded according to CTCAE v5.0.Quality of life - patient-reported outcomes will be evaluated using validated instruments (PRO-CTCAE, EORTC-QLQ-C30).

Exploratory Endpoints:

Out of field response - defined as a new radiographic response (per RECIST 1.1) in a non-irradiated lesion that was stable at enrollment. This endpoint is hypothesis-generating, as attribution to an abscopal effect is limited by the concurrent influence of ongoing systemic therapy.Blood collection: at baseline, 4 weeks post-radiation, and at the time of progression. At each timepoint, two 10 mL Streck Cell-Free DNA Blood Collection Tubes (BCT) will be collected for future analysis of circulating tumor DNA (ctDNA), cytokines, proteomics, metabolomics, and other serum/plasma biomarkers. In addition, two 10 mL Cell Preparation Tubes (CPT) with sodium citrate will be collected for isolation of peripheral blood mononuclear cells (PBMCs) for multiplex analysis of circulating immune cells including, flow cytometry (CyTOF), T cell receptor sequencing (TCR-seq) and single-cell RNA sequencing (scRNA-seq) for a minimal volume of 40 mL.

The primary hypothesis is that adding SBRT or hypofractionated radiotherapy to oligoprogressive lesions while continuing systemic treatment will yield a clinically meaningful extension of PFS. The trial protocol has been approved by the institutional Research Ethics Board, and the study will be monitored by the center’s clinical trials unit for compliance and safety.

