### Assessments and follow-up

The schedule of study assessments is summarized in **Table 2**. Baseline evaluations: At study entry, baseline tumor assessments are documented using imaging (CT, PET/CT and/or MRI) performed within 6 weeks prior to enrollment​. This imaging serves as the reference for measuring treatment response and progression going forward. Patients also complete baseline patient-reported outcome questionnaires (PRO-CTCAE, EORTC-QLQ-C30). Baseline blood samples are drawn and banked for exploratory biomarker studies.

**Table 2 T2:** Study timeline.

Required investigation	Pre-study (prior to enrolment)	Before 1st fraction of radiation	First follow-up after radiation (4 weeks ± 2 weeks)	Subsequent follow-up (every 12 ± 2 weeks until 104 weeks)
History and physical exam				
ECOG		X	X	X
Weight		X	X	X
Radiology				
CT CAP or PET/CT	Within ≤42 d			X
CT or MRI Brain (optional)	Within ≤42 d			If indicated
Specimen collection				
Blood collection		X	X	At the time of progression
Adverse events				
Survival status			X	X
CTCAE v5.0		X	X	X
Quality of life				
PRO-CTCAE		X	X	X
EORTC-QLQ-C30		X	X	X

Treatment and follow-up visits: During radiation delivery (which spans up to two weeks), patients are seen regularly for treatment management. An acute toxicity evaluation is performed at the end of the radiation treatment course (within a week of completing radiotherapy). Thereafter, follow-up visits are scheduled at approximately 8 weeks post-radiation, and then every 3 months for the first year, or until further disease progression. At each follow-up, a clinical examination and toxicity assessment are conducted. Adverse events are graded according to NCI CTCAE v5.0. In addition, patients complete PRO-CTCAE questionnaires to capture symptoms and side effects from the patient’s perspective, and the EORTC quality-of-life questionnaires are repeated at defined intervals (e.g. 3, 6, 12 months) to assess any changes in global health status and specific symptoms over time.

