### Statistical analysis

As reviewed in the literature, first-line therapy with immune checkpoint inhibitors results in a mPFS of 11.5 months (12). Our study was designed with the expectation that we would observe a median PFS improvement of about 7 months with addition of SBRT. Assuming an enrolment time of 12 months and follow-up of 24 months, 15% drop out and another 15% of screen failure, a sample size of 52 patients will achieve 85% power at 0.05 significance level to detect a median PFS of 7 months based on a two-sided, single arm log-rank test.

PFS/OS will be estimated using Kaplan-Meier (KM) method and presented graphically. The cumulative incidences of change in systemic therapy and acute/late toxicity will be estimated using the Aalen-Johansen method, where mortality without events of interest will be treated as competing event. Univariate Cox proportional hazard models will also be conducted to examine the association of PFS/OS with patient and tumor characteristics of interest, such as age, sex and the number of oligoprogressive lesions treated, BRAF mutational status, and type of first-line systemic therapy. Similarly, the univariate Fine-Gray competing risk models will be applied to examine the association of time to change in systemic therapy/acute/late toxicity with the patient and tumor characteristics of interests. Multivariable analyses (MVA) will also be conducted to determine the association if applicable. The change in QOL scores at follow ups from baseline (before SBRT) will be analyzed using linear mixed-effect models and the change in scores of >10 points would be deemed a minimal clinically important difference. The other categorical secondary outcomes (e.g. Out of field response, AE) will be summarized using frequency counts and proportion.

An interim analysis will be conducted after the first 25 patients have been enrolled and followed for at least 6 months, to assess safety and early efficacy trends. If ≥30% of patients experience grade 3 or higher toxicities deemed related to SBRT at that time, early termination of the trial will be considered.

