Toxicity data from trials combining radiation and ICIs have been reassuring. In the recently published phase 2 trial, which investigated SBRT in the oligoprogressive setting, 35% of patients in the SBRT arm received ICIs. Only two grade 3 toxicities were reported, with no grade 4 or 5 events observed (6). Additionally, a phase-1 dose escalation trial assessed the maximum tolerated dose of RT to patients with metastatic melanoma treated with single agent ipilimumab. The patients were treated with 6-8Gy in 2–3 fractions, and found no dose-limiting toxicities related to the radiation/ipilimumab combination (32).

Similarly, low toxicity rates were seen in other tumor types when combining SBRT and ICI treatment (33–35).

This study has several limitations. The most important is the single-arm design. Without a contemporaneous comparator, the contribution of SBRT to any observed prolongation of PFS cannot be isolated from the natural history of the disease or the effect of continued systemic therapy. Patients with oligoprogressive disease likely represent a more favorable prognostic subgroup than the general metastatic melanoma population, and a prolonged PFS in this selected cohort may partly reflect this selection rather than the effect of radiation. The outcomes should therefore be interpreted as hypothesis-generating. A positive efficacy signal would justify a randomized trial with a contemporaneous control arm to establish causal benefit. If the CURB-Melanoma trial demonstrates clinical benefit, it may serve as a foundation for a future phase III randomized trial comparing the current standard approach of systemic therapy modification versus SBRT with continued systemic therapy in patients with oligoprogressive melanoma. Such a trial would address a critical evidence gap and could definitively establish whether metastasis-directed therapy improves not only progression-free but also overall survival in this population.

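### The article's one toxicity criterion pools grades 3 to 5 and is applied once, near the end of accrual, so an SBRT-related death weighs no more than a grade 3 event

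*Protocol article*

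**What the plan says.** The protocol article, Statistical analysis, plans a single look: "An interim analysis will be conducted after the first 25 patients have been enrolled and followed for at least 6 months". Its purpose is "to assess safety and early efficacy trends". One criterion is attached to it: "If ≥30% of patients experience grade 3 or higher toxicities deemed related to SBRT at that time, early termination" is to be considered.

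The Assessments and follow-up section fixes the scale: "Adverse events are graded according to NCI CTCAE v5.0". On that scale a fatal event is grade 5, so it falls in the pooled category with grades 3 and 4.

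Outside the interim, the section on study design and endpoints says that "the study will be monitored by the center’s clinical trials unit for compliance and safety". No number or event that would prompt consideration of stopping is attached to that monitoring. The Treatment intervention section leaves the care of toxicity to usual practice, which concerns the patient and not the continuation of the trial. The article states no other toxicity criterion and no earlier look.

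**The concern.** A pooled percentage suits events that are common enough to be judged as a rate. It suits deaths poorly, because the number of treatment-related deaths that would call for a fresh look at the trial is far smaller than the number of grade 3 events that would. Here one threshold serves both, so a death moves the count by exactly as much as a single grade 3 event.

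The setting makes this more than a formality. Up to 10 progressing sites may be irradiated, sites irradiated before may be treated again if judged safe, and systemic therapy continues.

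The timing adds to it. A criterion applied only after 25 patients have 6 months of follow-up protects later patients only if many are still to be enrolled at that point. With the planned accrual, few are.

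**Working it through.** The article gives no count, error rate or power for this criterion, so there is no design figure to reproduce. The check is what the criterion requires, how it behaves, and when it acts.

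**Inputs from the article**
- Threshold 30%, grade 3 or higher, related to SBRT; 25 patients; 6 months of follow-up (Statistical analysis).
- Planned accrual (Abstract): "The trial aims to enroll 52 patients over 12 months with additional 24 months of follow-up".

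**Assumptions**
- Uniform accrual.
- True rates of SBRT-related death of 1%, 5%, 10% and 20%, for illustration. The article gives no such rate.

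**1. Count needed.** 0.30 × 25 = 7.5, so the smallest count is 8, and 8/25 = 32%. Seven patients are 7/25 = 28% and do not meet the criterion.

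**2. Behaviour by total rate of SBRT-related grade 3+ toxicity.** With X ~ Binomial(25, p), the chance that the criterion is met is P(X ≥ 8):

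| True rate p | P(X ≥ 8) |
|---|---|
| 10% | 0.002 |
| 20% | 0.109 |
| 25% | 0.274 |
| 30% | 0.488 |
| 40% | 0.846 |

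For the pooled rate this is ordinary behaviour for a 30% line: about an even chance at 30%, rising above it.

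**3. Behaviour if deaths were the only grade 3+ events.** P(at least one) = 1 − (1 − p)^25. P(at least two) subtracts a further 25p(1 − p)^24.

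| True death rate | At least one death in 25 | At least two | Criterion met |
|---|---|---|---|
| 5% | 0.72 | 0.36 | 0.00002 |
| 10% | 0.93 | 0.73 | 0.002 |
| 20% | 0.996 | 0.97 | 0.109 |

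These rows isolate the weight given to deaths. In practice grade 3 and 4 events would add to the count, and the chance of meeting the criterion would follow the table in step 2 at the total rate.

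**4. Timing.** The accrual rate is 52/12 = 4.33 per month. Patient 25 enters at 25/4.33 = 5.8 months, so the look falls at 5.8 + 6 = 11.8 months. Enrolment by then is 25 + 6 × 4.33 = 51 of 52. If accrual ran at half that rate (2.17 per month), it would be 25 + 6 × 2.17 = 38 of 52. Slower accrual leaves more patients to protect, but 13 would still have entered after patient 25 and before the look.

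**5. Denominator.** The criterion sentence says only that a share of patients must be affected. The natural reading is the 25. If it meant everyone enrolled at the look, 0.30 × 51 = 15.3 and 0.30 × 52 = 15.6, so 16 would be needed. Read literally, the 6-month requirement could also leave out patients who die before 6 months.

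**6. Cost of a single-death trigger.** At a true death rate of 1%, the chance of at least one SBRT-related death over 52 patients is 1 − 0.99^52 = 0.41.

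**The case against.** The strongest reply is that this is a condensed article. The criterion sentence is not false and contradicts nothing else in the article, and review of serious events and deaths is commonly set out in a full protocol, which is not shown. This stands to the extent that the article cannot show that the trial has no separate rule for deaths. It does not dispose of the point, because the article states the toxicity criterion itself, with a number and with the grades pooled, and that stated criterion can be judged.

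A reader might infer that up to seven treatment-related deaths would be tolerated, or that accrual would simply run on through them. The article does not support that. Meeting the criterion leads only to consideration of stopping, and missing it forbids nothing. The interim has a wider safety purpose than the threshold, and the trials unit monitors safety throughout. The seven-death example also needs the other 18 patients to be free of SBRT-related grade 3 or 4 events; one such event makes 8 and meets the criterion.

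A reader might also take the Discussion's toxicity paragraph as a forecast of no deaths, so that one death would refute the trial's premise. That paragraph reports two grade 3 and no grade 4 or 5 events in one cited phase 2 trial, in which 35% of the SBRT arm received checkpoint inhibitors. It gives no expected rate for this trial, and the stated hypothesis concerns PFS.

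Finally, a pooled grade 3+ line is a recognisable monitoring choice, and no text in the article singles out one death as the right trigger. That is fair, and is why the change below is an addition that prompts discussion and does not replace the existing line or force a stop.

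**Conclusion.** The point holds as a weakness in the written criterion that is cheap to repair. It is not an error of arithmetic, and it is not evidence that deaths would go unexamined. As stated, the criterion gives an SBRT-related death no separate weight, takes 8 of 25 patients to be met, and acts so late that it protects almost no accrual under the planned schedule. One or two deaths, the realistic case, do not meet it on their own.

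The count of 8 rests on taking the first 25 patients as the denominator. The month 11.8 and 51-patient figures rest on uniform accrual at the planned rate. The 93% and 0.2% figures rest on an assumed 10% death rate with no other grade 3+ events; they illustrate the weighting and are not predictions. That this is the one criterion is established for the article only.

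**What to change.** In Statistical analysis, keep the 30% line for grade 3 or higher and make three additions:

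1. A separately counted line: any SBRT-related grade 5 event, in any enrolled patient and at the time it occurs, leads to the same consideration of early termination. The timing is what gives protection during accrual; splitting the grades at the interim alone would not.
2. A statement that patients among the first 25 who die before 6 months count in both the numerator (if the event is SBRT-related) and the denominator at the interim.
3. Separate tabulation of grades 3, 4 and 5 at the interim.

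If the full protocol already has such a rule, citing it beside the 30% criterion resolves the point.

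The cost is a few sentences, with no added patients or procedures. The downside is an occasional review that proves unnecessary: a 41% chance of at least one over 52 patients at a true death rate of 1%. Such a review carries no automatic stop.

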## Discussion

The CURB-Melanoma trial evaluates whether SBRT to oligoprogressive lesions, combined with continued systemic therapy, extends PFS in metastatic melanoma. Prospective data in other solid tumors support this strategy: local ablation of limited progression has been shown to prolong duration of first-line therapy.

Oligoprogression, defined as isolated progression in a few lesions amid otherwise controlled disease (15), often reflects clonal resistance confined to select metastatic sites. In those settings, ablating oligoprogressive sites with SBRT prolongs the use of first-line therapy and delays the need for regimen change (16). The principle extends to melanoma: given the durability of responses to immune checkpoint inhibitors (ICIs), strategies that enable continuation of systemic therapy despite focal progression may provide substantial benefit.

The threshold of ≤10 oligoprogressive lesions was selected to maximize the eligible population in a disease where systemic options at progression are limited. Restricting enrollment to smaller thresholds would exclude patients with modest oligoprogression who have few alternatives and in whom continuation of first-line immunotherapy represents a meaningful clinical goal. This threshold is also consistent with contemporary trial design: SABR-COMET-10, a randomized phase III trial evaluating SBRT in patients with 4–10 oligometastatic lesions, is ongoing with results pending (17), and the ARREST phase I trial demonstrated that ablative radiotherapy is safe and feasible even in patients with more than 10 metastatic sites (18).

In metastatic melanoma, ICIs have substantially improved outcomes. Combination therapy with nivolumab and ipilimumab has yielded 10-year OS of 43% (HR 0.53, 95% CI 0.44-0.65) (12). However, resistance develops in many patients, with progression often confined to limited sites. Management typically involves switching therapies (e.g., BRAF/MEK inhibitors in patients with a driver mutation, TIL therapy, or enrollment into a clinical trials). However, maintaining the same systemic treatment while controlling the progressive sites is an appealing option. This approach has been described in several retrospective trials. For example, a multicentre study from France evaluated the role of SBRT in metastatic melanoma patients. The study included 69 patients, of which 29 had oligo-progression. The 1-year PFS was 41%, the mPFS was about 6 months, and the median time to change treatment was 5 months (19).

In another retrospective study, 101 metastatic melanoma patients treated for oligo-progression with SBRT and hyperthermia were followed up for a median of 15.3 months. Although PFS was not reported, the 12- and 24- month local control rates were promising - 93.5% and 88.3% respectively (20). In another study of metastatic melanoma patients treated with immunotherapy, 36 patients were treated for oligo-progression with a loco regional approach. The mPFS was 32 months (21). An observational trial by Chicas-Sett et al. published in 2022 assessed the effect of SBRT and continuation of immune-checkpoint inhibition beyond progression, among patients with metastatic non-small cell lung cancer or melanoma. Of the 50 patients analyzed, 19 had melanoma, and 12 were evaluable. The mPFS for the melanoma sub-group was 21.2 months (22). While the results of these trials are certainly hypothesis generating, they are all retrospective in nature, and are thus subjected to selection bias. They have also incorporated slightly different combinations (for example hyperthermia combined with RT) and have measured different end-points. The CURB-Melanoma is a prospective trial that will assess survival outcomes as well as patient-centered outcomes such as QOL.

Beyond local control for oligo-progressive lesions, SBRT can serve an immunological role, potentially overcoming resistance to first line systemic therapy. Radiation promotes antigen release, increases MHC expression, and can convert the tumor into an “*in situ* vaccine” (23). This effect is most famously illustrated in the abscopal phenomenon, where tumors outside the radiation field regress after local therapy. Though rare, abscopal responses have been reported in melanoma patients receiving radiotherapy with concurrent ICIs (24–26). The hypothesis-generating ‘RadVax’ trial, presented at the 2024 ASTRO Annual Meeting, demonstrated that patients with metastatic melanoma who had progressive disease following ICI treatment experienced both in-field and out-of-field durable responses after receiving SBRT to a single lesion. Immune profiling in this trial revealed dynamic changes in the immune landscape, including an increase in treatment-responsive effector-memory and central-memory CD8+ T cells following SBRT in responding patients - suggesting that local radiation may promote new T-cell priming and help overcome ICI resistance (27). Circulating tumor DNA, immune profiling, and the functional state of CD8+ T cells, including terminally exhausted subsets, are being developed as tools to stratify patients with melanoma and to track response to therapy (28, 29). The serial blood-based correlatives in CURB-Melanoma are intended to capture these measures and to generate hypotheses about which patients derive the greatest benefit from SBRT during first-line systemic therapy.

The rationale for adding SBRT to oligoprogressive disease applies across systemic therapy classes. Independent of the immunological effects of radiation, ablating the limited sites that have acquired resistance allows continuation of an otherwise effective regimen, whether immunotherapy or targeted therapy, and delays the switch to a less effective subsequent line. This local-control rationale is mechanism-agnostic and is the basis for the strategy in BRAF/MEK inhibitor-treated patients. The immunological rationale, including antigen release and abscopal responses, is most directly relevant to patients receiving immune checkpoint inhibitors, but radiation-induced immune priming is not exclusive to this group: BRAF/MEK inhibitors themselves increase antigen presentation and intratumoral T-cell infiltration, and radiation may further augment these effects. With first-line immunotherapy now preferred in most patients, the targeted therapy subgroup in this trial is expected to be small.

Clinical data from other sites of disease also support the synergy between RT and ICIs. For example, in the KEYNOTE-001 secondary analysis, NSCLC patients who had received prior radiation had significantly improved outcomes on pembrolizumab: median PFS increased from 2 to 6.3 months and OS from 5.3 to 10.7 months (30). The CURB-Melanoma trial builds on this evidence. By treating only the progressing lesions while continuing systemic therapy, it offers a way to eliminate resistant clones while leveraging ongoing immune surveillance. This approach avoids premature cessation of a therapy still active in most disease sites. It is analogous to strategies in NSCLC, where ablating progression allows patients to stay on targeted therapy for prolonged periods (16, 31). If similar durability can be achieved in melanoma, SBRT may have a defined role in managing ICI resistance in melanoma.

Toxicity data from trials combining radiation and ICIs have been reassuring. In the recently published phase 2 trial, which investigated SBRT in the oligoprogressive setting, 35% of patients in the SBRT arm received ICIs. Only two grade 3 toxicities were reported, with no grade 4 or 5 events observed (6). Additionally, a phase-1 dose escalation trial assessed the maximum tolerated dose of RT to patients with metastatic melanoma treated with single agent ipilimumab. The patients were treated with 6-8Gy in 2–3 fractions, and found no dose-limiting toxicities related to the radiation/ipilimumab combination (32).

Similarly, low toxicity rates were seen in other tumor types when combining SBRT and ICI treatment (33–35).

This study has several limitations. The most important is the single-arm design. Without a contemporaneous comparator, the contribution of SBRT to any observed prolongation of PFS cannot be isolated from the natural history of the disease or the effect of continued systemic therapy. Patients with oligoprogressive disease likely represent a more favorable prognostic subgroup than the general metastatic melanoma population, and a prolonged PFS in this selected cohort may partly reflect this selection rather than the effect of radiation. The outcomes should therefore be interpreted as hypothesis-generating. A positive efficacy signal would justify a randomized trial with a contemporaneous control arm to establish causal benefit. If the CURB-Melanoma trial demonstrates clinical benefit, it may serve as a foundation for a future phase III randomized trial comparing the current standard approach of systemic therapy modification versus SBRT with continued systemic therapy in patients with oligoprogressive melanoma. Such a trial would address a critical evidence gap and could definitively establish whether metastasis-directed therapy improves not only progression-free but also overall survival in this population.
